## 5.5 Justification of sample size.

A sample size of 10 participants was established for each group. The estimation of the sample size was based on the study by Sancho et al (10), in which the effect size was between 0.43 and 0.25 of the inter-straight distance for the supraumbilical and infraumbilical measurements. This sample size was calculated using G-Power 3.1 software with an alpha error of 0.05 and a power of 0.95. Considering a loss rate of 30%, a sample size of 14 participants per group was finally estimated.

## 5.6 Primary and secondary variables

The difference in inter-straight distance (DIR) before and after the intervention will be used as the treatment effect variable. The researcher who will carry out the measurements will be blinded and will not know to which group each participant belongs. The measurements will be carried out at the Navia Health Center, when space is available and with prior authorization from the Management of the Vigo Health Area.

- Measurement of DIR: Participants will be positioned in the supine position with knees bent at 90° with feet resting on the table and arms alongside the body. After being instructed to perform an abdominal crunch, subjects are asked to separate the head and elevate the shoulders until the scapula detaches from the table.

Ultrasound images will be recorded with an ultrasound scanner (GE Logic-e; 4-12 MHz, 39 mm linear transducer; B-mode), in a supine resting position and a muscle activation position (isometric contraction), 2 cm and 5 cm above the umbilicus.

To ensure that the two DIR measurements (2 cm and 5 cm above the umbilicus) are taken at the same location, the skin is marked with a water-soluble pen.

Ultrasound image collection will be performed immediately at the end of exhalation, as determined by visual inspection of the abdomen following the recommendations of Teyhen et al. (27) Special attention will be paid to the pressure exerted on the ultrasound probe on the patient to avoid reflexive response of the abdominal musculature (28).

For ultrasound image acquisition, the lower edge of the transducer will be placed over the mark made and moved laterally until the medial edges of both anterior rectus muscles can be visualized. The orientation of the transducer will be adjusted to

optimize image visualization. The collected ultrasound images will be exported to DICOM format for further measurement, analyzed by the same investigator, using a customized Matlab code (Image Processing Toolbox, Mathworks Matlab, USA) following the procedures described by Mota et al. (28). There is a good intra-evaluator reliability in DIR ultrasound images, with confidence interval values higher than 0.90(27).

These will be collected as independent variables:

- Group to which the patient is randomized (hypopressive abdominal exercises group and classic abdominal exercises group).
- Obstetric variables (maternal age, fetal weight, number of deliveries, weight gain during pregnancy): these variables will be administered by the midwives through their clinical history.

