## **1. Project background and justification**

Diastasis of the rectus abdominis (DRA) consists of the separation of the belly of the two rectus abdominis (inter rectus distance) along the linea alba with fibrous division and widening of the same (1,2). The functions of the linea alba are diverse, on the one hand, to maintain the anterior rectus abdominis close together, to guarantee the stability of the spine, pelvis and pelvic floor and to intervene in the function of the abdominal muscles since it serves as an anterior anchorage for them (3 -5).

During pregnancy, ARD occurs physiologically due to hormonal elastic changes in the connective tissue and mechanical stresses on the abdominal wall produced by the growth of the fetus and the displacement of abdominal organs (6). It usually appears between the second and third trimester (6) and resolves spontaneously between 1 and 8 weeks after delivery (7,8). In some women, this spontaneous resolution does not occur after delivery, and it then becomes a pathologic condition that may persist for years after delivery (6,7).

In the scientific literature, the most studied exercise to check the behavior of the linea alba has been the abdominal crunch, finding in most cases a decrease in the inter-straight distance (IRD) compared to rest (9 -13). Mota et al. (12) and Chiarello et al. (9) show that, in women with children, this exercise causes a more accentuated decrease in IRD than in nulliparous women. Regarding transverse activation, an exercise recommended for the treatment of ARD (14,15), it causes an increase in DRI in most studies (10,12,16), which could be due to the orientation of its fibers that would help to tighten and widen the linea alba (1,12,17), favoring optimal functioning due to the tension created (13).

The abdominal hypopressive technique was described in 1980 by Marcel Caufriez, a Belgian physiotherapist (18). According to Caufriez, hypopressive exercises, initially intended for women in the postpartum period, produce a drop in abdominal pressure through diaphragmatic suction and this in turn causes contraction of the pelvic floor muscles and deep abdominal muscles (18,19).

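### Section 5.5 bases 0.95 power on effect sizes from a study the protocol groups with contraction-versus-rest work, which do not support that power for a between-group difference in 6-week DIR change

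*Protocol*

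**What the plan says.** **Sizing (Protocol 5.5).** "A sample size of 10 participants was established for each group". The basis is reference 10, "in which the effect size was between 0.43 and 0.25 of the inter-straight distance for the supraumbilical and infraumbilical measurements". The number was "calculated using G-Power 3.1 software with an alpha error of 0.05 and a power of 0.95". Then: "Considering a loss rate of 30%, a sample size of 14 participants per group was finally estimated". The effect-size metric, the test, the sidedness, any SD and any pre-post correlation are not given.

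**Endpoint (Protocol 5.6, 5.7, 5.9).** The treatment-effect variable is the pre-post difference in DIR. The programmes last 6 weeks, and the main analysis compares the two groups' change by a repeated-measures method. Images are taken "in a supine resting position and a muscle activation position (isometric contraction), 2 cm and 5 cm above the umbilicus". The skin-marking instruction, "To ensure that the two DIR measurements (2 cm and 5 cm above the umbilicus) are taken at the same location", names no other site.

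**What the protocol says about reference 10 (section 1).** The background discusses the abdominal crunch, "finding in most cases a decrease in the inter-straight distance (IRD) compared to rest (9 -13"), a citation range that includes reference 10. The same section says the authors know of only two randomised trials of exercise programmes on this outcome, references 25 and 26. One, of 16 weeks, found no effect. The other, of 8 weeks, found a decrease. No magnitude is given for either.

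**The concern.** A sample-size justification needs an effect on the comparison that will be tested. Here that is how much more DIR changes over 6 weeks under one active programme than under another. By the protocol's own account, reference 10 belongs with studies of how the distance changes in a woman while she contracts, relative to rest. The two quantities have different numerators (an immediate response versus a lasting change, within women versus between groups). They also have different denominators, because the SD of an acute response need not resemble the SD of a 6-week change. A standardised effect from one cannot be carried to the other without an argument, and 5.5 gives none.

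What is at stake is how a null result is read. If 0.95 power is taken at face value, a non-significant comparison looks like good evidence that the programmes are equivalent. With about 10 women per group it would not be.

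**Working it through.** **1. Reproduce the plan's figure.** Inputs from 5.5: effect 0.43 (upper value), alpha 0.05, power 0.95, 10 per group (N = 20). Assumed because not stated: 0.43 is Cohen's f, two time points (m = 2), correlation ρ = 0.5, and the group-by-time interaction test.

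- λ = f² × N × m / (1 − ρ) = 0.43² × 20 × 2 / 0.5 = 0.1849 × 80 = 14.79, on 1 and 18 df.
- Power = 0.953, and N = 20 is the smallest balanced total reaching 0.95. The stated 10 per group reproduces.

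This depends on the assumptions. With f = 0.43, the total needed is 38 at ρ = 0 and 14 at ρ = 0.7. Other readings also give 20: 0.43 taken as eta-squared in a one-way ANOVA (power 0.956), or the midpoint (0.43 + 0.25)/2 = 0.34 taken as f with ρ = 0.7 (power 0.960). The route actually used cannot be recovered from the document.

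Losses: 10 / 0.7 = 14.29. The stated 14 is rounded down, which is immaterial here.

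**2. Put the assumed effect on the scale of the endpoint.** For a two-group comparison of change, the noncentrality is d × √(n/2), where d is the between-group difference divided by the SD of change. With λ = 14.79:

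- √14.79 = 3.85, so d = 3.85 × √(2/10) = 3.85 × 0.447 = 1.72.

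**3. Check directly, without the f and ρ assumptions.** Two-sample t, two-sided 0.05, n = 10 per group, 18 df, solved from the noncentral t:

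- 95% power: d = 1.71
- 80% power: d = 1.32
- If all 14 per group were analysed, 95% power: d = 1.42

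Steps 2 and 3 agree. Ten per group at 95% power means a difference of about 1.7 SD of change, however the software inputs were chosen.

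**4. What a null result would show.** The 95% interval for the between-group difference has half-width of about t(0.975, 18) × √(2/10) = 2.101 × 0.447 = 0.94 SD of change. An observed difference of zero would still be compatible with almost one SD either way.

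**5. Sensitivity to the lower cited value.** With f = 0.25 in the step 1 set-up, λ = 0.0625 × 80 = 5.0, power at N = 20 is 0.56, and N = 54 (27 per group) would be needed. This shows only how strongly the power statement depends on the input. It is not an estimate of the true power.

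**6. Compare with the protocol's own evidence.** Section 1 cites one programme trial with no effect and one with a decrease, neither with a size. Nothing there supports a 1.7 SD advantage of one active programme over another.

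**The case against.** **The arithmetic is right.** This stands. Ten per group follows from 0.43 under ordinary software settings, and the point is not a miscalculation.

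**The detectable difference only restates the input.** Largely true: 1.72 SD is f = 0.43 on another scale. It does not measure the gap between an acute and a trained response. It does show what the protocol is implicitly assuming about its endpoint, which 5.5 does not reveal.

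**Reference 10 has not been seen.** This also stands. Section 1 describes references 9 to 13 together and says "in most cases" of them only as a group; it does not say which contrast gave 0.43 or 0.25. The count of two programme trials covers randomised trials only. That the figures are acute responses is a well-supported inference, not an established fact.

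**Proxy data are normal when little exists, and DIR is also recorded during contraction.** Fair, but a proxy needs an argument linking it to the endpoint, and imaging in contraction does not turn a contraction-versus-rest effect into a between-group 6-week change.

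**Stronger readings to resist.** A reader might infer from 5.5 that an infraumbilical result is promised and cannot be delivered. The protocol does not support this: 5.5 is describing another study's measurements, no infraumbilical outcome is declared, and nothing planned is lost. Nor does it show that the infraumbilical figure drove the sample size. The plan's number reproduces from 0.43 alone, and pairing 0.25 with the infraumbilical site rests only on word order. A reader might also take 0.43 and 0.25 as between-group Cohen's d and quote power of 15% and 8% at 10 per group. The metric is not stated, so those figures cannot be attributed to the plan.

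**Conclusion.** The point holds in this form: the effects cited in 5.5 do not support 0.95 power for the trial's main comparison. Ten analysed per group gives 95% power only for a between-group difference of about 1.7 SD of the 6-week change, and 80% for about 1.3 SD. The protocol cites no training data for a difference that large. These figures assume a two-sided 0.05 test, equal groups, roughly normal change scores and a simple two-sample comparison of change.

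The conclusion about the source rests on the protocol's own description of reference 10 and should be confirmed against the paper. The finding does not show that the trial is underpowered for its true effect, which is unknown. The difference in measurement sites between 5.5 and 5.6 is a minor wording matter. The trial can run as sized, but its stated power should not stand.

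**What to change.** In 5.5:

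- Stop presenting the reference 10 effects as the basis for 0.95 power on this endpoint. If they are kept as background, say which contrast they describe, after checking the paper.
- State what the fixed sample can detect: with 10 analysed per group and two-sided 0.05, a between-group difference in 6-week DIR change of about 1.7 SD of change at 95% power and 1.3 SD at 80%. Tie this to one named supraumbilical site (2 cm or 5 cm) and one muscle state (rest or contraction). If an SD of change is available, give the difference in millimetres as well.
- Add that a non-significant result will not be read as equivalence of the programmes.
- Remove the infraumbilical mention, or say that it is not relevant to this trial because 5.6 scans only above the umbilicus. No extra image is needed; one would add another outcome to a plan that already has two sites and two states.

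The cost is a few sentences, with no added participants or procedures. This does not make the sample size justified by an expected effect. It replaces an unsupported power claim with an honest statement of what the sample can show, and the stated justification will look less favourable.

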##### *Description of the intervention*

*Group 1:* Classic abdominal strengthening exercises (curl-ups, sit-ups and leg-rise), balance exercises, general mobility and upper limb strengthening exercises.

*Group 2:* Hypopressive abdominal exercises, balance exercises, general mobility and upper limb strengthening exercises.

In both groups the exercise programs will have a duration of 6 weeks, with a timing of 2 days per week (1 hour per session), making a total of 12 sessions. The interventions will be carried out in the Navia Health Center, when there is availability of space and prior authorization of the Management of the Health Area of Vigo.

5.8 Timeline and expected completion date. Distribution of tasks among the members of the research team.

The study is expected to begin and end in 2022, provided that health conditions permit and the ethics committee approves. The distribution of tasks of the investigators is as follows:

- [name]: Theoretical development of the project and organization of the rest of the researchers. Randomization of the participants to the treatment groups. Statistical analysis of the data and participation in the writing of the research article derived from this research.
- [name]: In charge of carrying out the exercise program in the classical abdominal strengthening group. Participation in the writing of the article derived from this research.
- [name]: In charge of carrying out the exercise program in the hypopressive abdominal exercises group. Participation in the writing of the article derived from this research.
- [name]: Participation in the theoretical development of the project, in the statistical analysis of the data and in the writing of the article derived from this research. In charge of carrying out the evaluations (pre and post intervention) through ultrasound measurements.
- [name]: Recruitment of participants and collection of obstetric variables.
- [name]: Recruitment of participants and collection of obstetric variables.
- [name]: Recruitment of participants and collection of obstetric variables.
- [name]: Recruitment of participants and collection of obstetric variables.
- [name]: Recruitment of participants and collection of obstetrical variables

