### 5.9 Statistical analysis plan

The dependent variable (DIR) will be analyzed using standard normality tests (Shapiro-Wilk test) to find the normality criteria (29). In the case of a normal distribution of the data, the difference in DIR will be analyzed through an analysis of variance (ANOVA).

The Pearson or Spearman correlation coefficient will be used for the analysis of obstetric variables and their relationship with the DIR.

The main analysis will be based on the difference in DIR pre-post intervention and the comparison between groups by means of a repeated measures analysis. A significance level of  $p < 0.05$  will be established for all variables.

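### Section 5.6 names one treatment effect variable but measures it four ways, and neither 5.6 nor 5.9 fixes which measure, or which single test, decides the hypothesis

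*Protocol*

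**What the plan says.** Section 2 states a single hypothesis: the hypopressive programme reduces the distance more than the classic programme. It names no measurement site and no muscle state.

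Section 5.6, which is headed as the place for primary and secondary variables, names one variable: "The difference in inter-straight distance (DIR) before and after the intervention will be used as the treatment effect variable". It then describes images taken "in a supine resting position and a muscle activation position (isometric contraction), 2 cm and 5 cm above the umbilicus". The activation task is a crunch: "After being instructed to perform an abdominal crunch, subjects are asked to separate the head and elevate the shoulders until the scapula detaches from the" … Read together, the crunch is held while the image is taken. None of the four measures is called primary or secondary.

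Section 5.9 describes the main analysis in one sentence: "The main analysis will be based on the difference in DIR pre-post intervention and the comparison between groups by means of a repeated measures analysis". It does not say how site and state enter that analysis. The significance level of 0.05 "will be established for all variables", with no order of testing and no adjustment.

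**The concern.** A reader of the final report needs to know in advance which number decides the hypothesis. Here four numbers could do so, and the analysts could choose among them, or among several terms of one model, after seeing results. Two things are at stake. The 5% error rate holds for the main hypothesis only if one test was fixed beforehand. And if the resting and contracted measures, or the two sites, point in different directions, the protocol has no rule for which one counts.

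A detailed multiplicity procedure can be left to a separate analysis plan. The choice of primary outcome cannot easily be: it belongs in the section on primary and secondary variables, and 5.9 is itself headed as the statistical analysis plan.

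**Working it through.** **Count of measures (5.6).** 2 states × 2 sites = 4.

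**The plan's own figure (5.5).** Stated inputs: alpha 0.05, power 0.95, effect size between 0.43 and 0.25, 10 per group. I read 0.43 as Cohen's f for the group-by-time term with 2 groups and m = 2 times, and assume a correlation of 0.5 between times. The protocol states neither the metric nor this correlation.
- λ = f²·N·m/(1−ρ) = 0.43² × 20 × 2/0.5 = 14.8, on 1 and 18 degrees of freedom. Power is 0.953, so N = 20 (10 per group) is reproduced.
- With f = 0.25, power at N = 20 is 0.562, and 95% power needs N = 54.

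The stated size therefore fits one test at 0.05 with the larger effect. It does not show which measure that test uses. Section 5.5 speaks of supraumbilical and infraumbilical effects, but both planned sites are above the umbilicus, and rest and contraction are not distinguished.

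**False-positive rate if all four are tested at 0.05 and any one counts.**
- Independent: 1 − 0.95⁴ = 0.185.
- Correlated: 100,000 simulated trials per setting, four equally correlated outcomes with no true difference, two-sample t tests, 10 per arm. With two groups and two times, a t test on the change is equivalent to the group-by-time F test.

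| Common correlation | P(at least one p<0.05) | Multiple of 5% |
|---|---|---|
| 0 | 18.5% | 3.7 |
| 0.3 | 17.4% | 3.5 |
| 0.5 | 15.6% | 3.1 |
| 0.7 | 13.2% | 2.6 |
| 0.8 | 11.7% | 2.3 |
| 0.9 | 9.7% | 1.9 |
| 0.95 | 8.2% | 1.6 |

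With 14 per arm the results are nearly the same (15.8% at 0.5, 9.5% at 0.9). Equal correlation is not critical: a pattern with 0.9 between one pair type, 0.6 between the other and their product elsewhere gives 12.6%; 0.7 and 0.3 give 15.7%.

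**One direction only.** False positives that favour the hypothesised arm run from 1 − 0.975⁴ = 9.6% (independent) to 4.9% (correlation 0.9). The comparator for a single two-sided 0.05 test is 2.5%.

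**Two ways to hold 5%.**
- One named measure and one group-by-time test: 5%, and N = 20 stands.
- All four with Bonferroni, 0.05/4 = 0.0125 each: 1 − 0.9875⁴ = 4.9% if independent. Power per test at N = 20 falls from 0.953 to 0.843. 95% power needs 28 evaluable women, 14 per group, hence 14/0.7 = 20 per group after 30% loss, against the 14 planned.

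**The case against.** **The inflation is not planned.** A reader might infer that the trial's false-positive rate is two to nearly four times 5%. The documents do not support that as a fact. Section 5.9 refers to DIR in the singular and to a repeated measures analysis. It does not announce four tests or say that one significant result is enough. One model with site and state as within-woman factors and one pre-named group-by-time test would keep 5%. The measures come from the same woman on the same day at sites 3 cm apart, so correlation may be high, and above 0.9 the rate is less than double. All this stands, and it makes the figures conditional. It does not remove the gap, because 5.9 names no such test. A model of that kind also offers group-by-time terms crossed with site, with state and with both. Pooling would average rest with a contraction that section 1 describes as usually narrowing the distance.

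**Smaller may not be better.** A reader might also infer, from the statement in section 1 that "it causes an increase in DRI in most studies", that a smaller contracted distance is not clearly a benefit. That sentence concerns transversus activation. The task measured in 5.6 is a crunch, for which section 1 reports narrowing in most cases. Both statements describe an immediate response, not change over six weeks. I do not rely on this argument.

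**Practice of the test task.** Only Group 1 trains curl-ups and sit-ups, which resemble the crunch used for the contracted image. A reader might take this as a demonstrated bias. No passage says that practice alters the contracted distance apart from tissue change, and if it narrowed it in Group 1 it would work against the hypothesis. It is an inference about interpretation, unrelated to the error rate. What remains is a reason to prefer a resting measure.

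**Conclusion.** The point holds in this form: one treatment effect variable is named, four measures stand behind it, and the protocol fixes neither a primary measure nor a single deciding test while applying 0.05 throughout. Should the four be tested separately with any one taken as the answer, the two-sided false-positive rate is about 18.5% if independent, 16% at correlation 0.5, 10% at 0.9 and 8% at 0.95. Those values assume equal correlations, which the protocol does not give, and a decision rule that it does not state. They show what the open choice allows, not what the plan prescribes. A single pre-named group-by-time test would be at 5%.

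**What to change.** In 5.6 and 5.9, name one primary outcome and one test. For example: *The primary outcome is the pre-post change in resting DIR at 2 cm above the umbilicus. The groups are compared by the group-by-time term of a repeated measures analysis with two groups and two times, two-sided alpha 0.05. Resting DIR at 5 cm, and DIR during the held crunch at 2 cm and 5 cm, are secondary. They are reported as estimates with 95% confidence intervals, or tested with Holm adjustment.*

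Nothing in the protocol favours 2 cm over 5 cm. Either is acceptable if the sponsor fixes it and gives a reason. A resting measure avoids a test task that resembles an exercise trained in only one group. Section 5.5 should then say that the effect size of 0.43 refers to the chosen measure.

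Timing: section 5.8 expects the study to start and finish in 2022, so a change before the first participant may no longer be possible. The choice should be documented before outcome data are examined by group. Section 9 gives a natural limit, since the group column is to be filled in only at the end of the study.

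Cost: a few sentences, with the stated 10 per group unchanged. The downside is that a significant result at another site or in the other state can no longer carry the conclusion. Keeping all four as co-equal outcomes under Bonferroni would instead mean 20 per group after losses, on the assumptions above.
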